**A Yoga Exercise Intervention Designed for Women with Knee Osteoarthritis**

**Protocol**

**Introduction**

Over 4 million Canadians endure a form of arthritis (1). This number will escalate because, as a nation, we are getting older and heavier at an alarming rate (1). Arthritis is the single greatest cause of chronic disability among community-dwelling older adults, by painfully restricting mobility in daily life (2). The most common arthritis, osteoarthritis (OA), affects 10% of Canadian adults (1). Osteoarthritis results from excessive and abnormal loads that degrade cartilage and bone, most frequently in the knee. Adding to the complexity of treatment, knee OA rarely occurs in isolation. This population has elevated incidences of cardiovascular and gastrointestinal disorders and depression (1).

Keeping older adults with knee OA moving is critically important but not straight-forward. Systematic reviews and clinical practice guidelines confirm that exercise is critical in knee OA treatment (3-5). Exercise reduces symptoms, co-morbidity and improves physical function (3-5). In fact, the effects of aerobic and strengthening exercise on pain are equivalent to medication (5). However, important caveats exist. Generic exercise prescription in large samples produces mediocre findings in terms of pain and physical function (3). It is important to note that these exercise programs did not benefit from data that would properly dose the type, intensity, repetition and biomechanical load of the exercise for people with knee OA.

There are concerns that improperly dosed exercise can accelerate knee OA progression. High loading repetition, a feature of walking programs for example, is linked to greater intensity knee pain in people with knee OA (6). Exercise programs that require footwear may not be ideal because shoes elevate the mechanical loads within the knee. In particular, the knee adduction moment was increased by 38% when 68 subjects were wearing running shoes compared to barefoot (7). The knee adduction moment reflects the proportion of load placed on the medial knee compartment that is most commonly degraded in this disease. Longitudinal studies clearly demonstrate that the knee adduction moment predicts progression noted on radiographs (8) and on magnetic resonance imaging scans (9). Finally, while quadriceps strengthening improved symptoms in many samples with knee OA, concerns have been raised about the potential for traditional strengthening programs to increase the contact forces that may contribute to acceleration of knee OA (10, 11). These experts recommend that strengthening exercises must elicit muscle activation patterns, while maintaining ideal alignment of the lower extremity to minimize the knee adduction moment.

Studies showing that generic exercise programs improved pain and mobility in people with knee OA provide confidence that exercise is fundamental to the management of this disease. Improving exercise programs to minimize biomechanical risks specific to knee OA may enhance the benefits of exercise for this population. Yoga offers a foundation of static postures that improve muscle strength and joint flexibility, while eliminating repetition, footwear and, if properly analyzed, the knee adduction moment.

Yoga is an exercise activity that emphasizes controlled, fluid movements through a variety of static postures. Many yoga postures challenge and strengthen musculature of the lower extremity, while minimizing some potential negative effects that other exercise programs pose for people with knee OA. For example, running is an activity that includes large and repetitive loads on the knee, which may not be the best-suited activity for individuals with knee OA. Yoga has beneficial effects on various aspects of quality of life, including improved cardiorespiratory health, body awareness, well-being and mental health. Further, yoga has been shown to improved strength, balance, flexibility, pain, and disability in older adults and individuals with knee OA (12) (13) (14) (15) (16) (17). For example, a pilot study consisting of 7 women over age 50 years with symptomatic knee OA implemented an 8-week program of modified yoga postures. Each week participants attended one 90-minute weekly class. Participants reported improvements in knee pain, physical function and mental health, demonstrating that yoga holds great potential as a treatment option for older, yoga-naive women with knee OA (16).

We recently completed a biomechanical analysis of ten common yoga postures that emphasize lower extremity strengthening, including squats, lunges and balancing postures in 30 young women [not yet published]. These analyses focused on the knee adduction moment and muscle activation patterns to identify postures that did not overload the medial knee while requiring enough muscle activity to result in strengthening. Of the ten yoga postures, eight produced negligible knee adduction moments and all required muscle activations that would facilitate strengthening of the quadriceps and hamstrings [not yet published]. These data provide the foundation for an intervention that emphasizes the eight yoga postures that result in negligible knee adduction moments.

Research Question & Hypotheses

The primary objective of this study is to determine whether a yoga exercise intervention will improve the strength of the musculature that surrounds the knee without increasing knee pain in women with knee osteoarthritis (OA). A secondary objective is to determine whether a yoga exercise intervention will reduce the knee adduction moment during gait, improve mobility performance, and improve cardiovascular fitness.

Study participants will experience increased strength in the musculature surrounding the knee and reduced knee pain after completing the yoga intervention. As well, study participants will demonstrate a reduced knee adduction moment during gait, improved mobility performance, and improved cardiovascular fitness after completing the yoga intervention.

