**Study Design and Methods**

This intervention study features a repeated measures design. Outcome measures will be assessed at McMaster University before and after a 12 week intervention. The yoga exercise intervention will be delivered at a yoga studio in downtown Hamilton, Ontario. This proof of principle study will aim to provide preliminary data supporting the use of a yoga exercise intervention in a sample of women with knee OA.

Participants

Fifty community-dwelling women, 50 years of age and older, who meet the American College of Rheumatology (ACR) criteria for clinical knee OA will be recruited to participate in this study. The ACR clinical criteria require 3 of the following:

- Knee pain on most days of the week,
- Less than 30 minutes of morning stiffness,
- Crepitus with active range of motion,
- Bony enlargement,
- Bony tenderness to palpation, and
- Signs of inflammation (warmth, swelling).

*Inclusion and Exclusion Criteria*

Women were selected because incidence of knee OA is two times greater among women than men over the age of 50 years (18-20). Muscle weakness is of particular concern in women with knee OA because their absolute muscle strength is lower compared to men, and therefore women are closer to the critical thresholds of strength required for activities of daily living (21). Finally, women report pain secondary to knee OA more frequently than men (20) perhaps because the pain experience is different (22). The incidence and prevalence of knee OA increases with age, particularly in women (18, 20, 23-25).

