- The Knee Osteoarthritis Outcome Score (KOOS) is a patient-administered, 42 item questionnaire.  Study participants are asked to answer questions on a 5-point Likert scale, which takes approximately 10 minutes to complete.  The KOOS consists of 5 subscales:  pain, other symptoms, activities of daily living (ADL), function in sport and recreation and knee-related quality of life (QOL).  The questionnaire results in a normalized score out of 100 for each subscale, where 100 indicates no symptoms and 0 indicates extreme symptoms. The questionnaire relies on subject’s recall from the previous week.

The KOOS has been used in persons 13-79 years of age. The KOOS reference values are available from various sample populations including; age/sex based samples (33) (34), active soccer players (35), and male and female patients post anterior cruciate ligament reconstruction (36). The KOOS has a high test-retest reliability demonstrated by intra-class correlation coefficients of 0.80-0.97 for the Pain subscale, 0.74-0.94 for the Symptom subscale, 0.84-0.94 for the ADL subscale, 0.65-0.92 for the Sport/Rec subscale and 0.60-0.91 for the QOL subscale in patients with knee osteoarthritis (OA) (37). The minimal detectable change values for patients with knee OA are 13.4 for Pain, 15.5 for Symptoms, 15.4 for ADL, 19.6 for Sport/Rec, and 21.1 for QOL (38). Currently, the minimal clinically important change value is suggested to be 8-10 for the KOOS, proving the scale is sensitive to change (38). The KOOS has been reported to detect change following surgical procedures including; ACL reconstruction, meniscectomy, cartilage repair procedures, tibial osteotomy, total knee replacement and non-surgical procedures including; physical therapy, as well as nutritional and pharmaceutical interventions (39). The KOOS presents an internal consistency range (Cronbach’s α) of 0.65–0.94 for Pain, 0.56–0.83 for Symptoms, 0.78–0.97 for ADL, 0.84–0.98 for Sport/Rec and 0.71–0.85 for QOL in patients with knee OA (38). The KOOS has demonstrated convergent and divergent construct validity when compared against numerous instruments including the different subscales of the Short Form-36 and the Lysholm knee scoring scale (38).

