*Baseline Measures: MacMobilize Laboratory at McMaster University, Hamilton*

1. Written, informed consent
2. Anthropometric Measurements
3. Resting Heart Rate and Blood Pressure
4. Instrumentation & Biomechanical Analyses (Gait and Yoga)
5. Mobility Performance Measures
6. Strength Assessment
7. Questionnaire: KOOS
8. YMCA protocol

This laboratory visit will require 2.5 hours to complete.

*Yoga Intervention: De La Sol Yoga at [name], Hamilton*

- 12-week intervention
- Requesting attendance to 3 supervised classes each week

Each yoga class will be 1 hour.

*Follow-up Measures*

1. Anthropometric Measurements
2. Resting Heart Rate and Blood Pressure
3. Instrumentation & Biomechanical Analyses (Gait and Yoga)
4. Mobility Performance Measures
5. Strength Assessment
6. Questionnaire: KOOS
7. YMCA protocol
8. Stipend

This laboratory visit will require 2.5 hours to complete.

Sample Size Estimation

Systematic reviews of the effectiveness of resistance training for improving self-reported physical function and isometric knee strength in knee OA had average effect sizes of 2.11 and 0.41 respectively (5). Given the lower effect size (0.41) and a Type I error = 0.05 on a 1-tailed test (based on strong evidence of improvement), a sample of 39 participants is necessary to yield 80% power to detect a significant effect. We aim to recruit 45 participants to account for drop-outs and losses to follow-up.

Statistical Analyses

Descriptive statistics will be determined for all of the outcome measures. Repeated measures analysis of variance will be used to determine if changes in the primary and secondary outcome measures as a result of the yoga exercise intervention. The p value will be set at p<0.05.

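### The primary objective asks that knee pain not increase, the hypothesis says pain falls, and the planned test for difference serves only the hypothesis

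*Protocol*

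**What the plan says.** Under Research Question & Hypotheses, the primary objective is whether the programme "will improve the strength of the musculature that surrounds the knee without increasing knee pain in women with knee osteoarthritis (OA"). The hypothesis under the same heading is stronger on pain: "Study participants will experience increased strength in the musculature surrounding the knee and reduced knee pain after completing the yoga intervention".

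Pain is a primary outcome, measured by the KOOS, "where 100 indicates no symptoms and 0 indicates extreme symptoms", so a negative change is a worsening. In the same description, "the minimal clinically important change value is suggested to be 8-10 for the KOOS". That figure is given as a property of the scale and is not tied to any decision.

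Statistical Analyses provides descriptive statistics and one inferential method: "Repeated measures analysis of variance will be used to determine if changes in the primary and secondary outcome measures", with a threshold of p<0.05. No criterion is given for deciding that pain has not increased. Sample Size Estimation uses an effect size of 0.41 for isometric knee strength, one-tailed, and arrives at 39 participants. Pain does not enter that calculation. The study is described as before-and-after and as a proof of principle.

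**The concern.** Two different questions are put to one primary outcome. No increase in pain is a statement that any worsening is too small to matter, and it needs a limit to be judged against. Reduced pain is a statement of difference, which an ANOVA can test. The named analysis answers the second question only.

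Three outcomes are possible. A significant fall in pain meets both statements. A significant rise counts against both. A non-significant change leaves the objective undecided, because failing to reject a zero difference is not evidence that pain stayed level, and noisier data make non-significance more likely. The third outcome is where the plan has no rule. The Introduction itself raises the concern that exercise can aggravate knee OA, so the pain half of the objective is not a formality.

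**Working it through.** **Inputs from the protocol.** Effect size 0.41, one-tailed alpha 0.05, 80% power, n = 39 (Sample Size Estimation); p<0.05 (Statistical Analyses); important change of 8 to 10 KOOS points (Primary Outcome Measures, Pain).

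**Assumed.** SD of the individual change in KOOS Pain of 10, 15 or 20 points, and 39 completers. The protocol gives no SD of change.

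**1. The protocol's own figure.** For a paired t-test with d = 0.41 and one-sided 0.05, the noncentral t gives power 79.8% at n = 38 and 80.8% at n = 39. The stated 39 reproduces. It concerns strength alone.

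**2. What a non-significant pain result leaves open.** With two time points, the ANOVA F statistic is the square of the paired t, so the test is two-sided. The half-width of the 95% CI is h = t(0.975, 38) × SD/√39 = 2.024 × SD/6.245. A worsening that just misses significance has mean -h and a CI running from -2h to 0. The limit 2h reaches 8 points at SD = 8 × 6.245/(2 × 2.024) = 12.3, and 10 points at SD = 15.4.

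**3. Chance of missing a true 8-point worsening.** The noncentrality is 8 × √39/SD. The chance is the probability that |t| stays below 2.024.

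**4. Power of a margin rule.** Margin 8, true change 0, one-sided 0.025. The distance from truth to the tested value is again 8 points, so the noncentrality is the same as in step 3.

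| Assumed SD of change | 10 | 15 | 20 |
|---|---|---|---|
| Half-width h (points) | 3.24 | 4.86 | 6.48 |
| CI limit if just non-significant, 2h | 6.5 | 9.7 | 13.0 |
| Noncentrality for 8 points | 5.00 | 3.33 | 2.50 |
| True 8-point worsening missed | 0.2% | 10% | 32% |
| Power of margin-8 rule | 99.8% | 90% | 68% |
| Completers for 80% power, margin 8 | 15 | 30 | 52 |

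With 39 completers, the margin-8 rule keeps 80% power up to an SD of about 17.4.

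**5. What the margin rule lets through.** If the true worsening is 4 points, the distance to the margin is 8 - 4 = 4 and the noncentrality is 4 × √39/SD. The rule then declares no increase in 68%, 37% and 23% of trials with a 95% CI, or 79%, 50% and 34% with a 90% CI. The ANOVA is non-significant for the same 4-point worsening in 32%, 63% and 77%. A 4-point worsening is therefore no argument for the margin rule, since a margin of 8 treats it as tolerable. The case for the rule rests on worsening of 8 points or more.

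**The case against.** The strongest reply is that the test matches the stated hypothesis, and a significant reduction would satisfy the objective too. That is right: the gap exists only when pain does not fall significantly. It would be too strong to say that the trial cannot answer half of its primary question, because a confidence interval from the same data can settle it. At an SD of change below about 12.3, any non-significant result with 39 completers already excludes an 8-point worsening.

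A reader might infer that the investigators intend to treat a non-significant result as proof of no harm. The protocol nowhere says so. A reader might also infer, from the one-tailed test, that the analysis is blind to worsening. That test appears only in the strength-based sample size. The ANOVA is two-sided and can detect worsening.

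It can also be said that margins and interval rules are commonly left to the SAP, which is not at hand. As to the margin alone, that is fair. But the protocol itself states two different pain questions and fixes the single test and threshold, and an SAP should not have to choose which primary question is meant.

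Finally, "This proof of principle study will aim to provide preliminary data supporting the use of a yoga exercise intervention". This lowers the stakes, but it does not tell the reader what result would meet the primary objective.

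**Conclusion.** The point holds in this form: objective and hypothesis disagree on pain, and the only planned inference serves the hypothesis. Unless pain falls significantly, the p-value cannot establish that it did not increase. The size depends on an SD that the protocol does not give. At SD 10 the consequence is slight, since even a just non-significant result excludes an 8-point worsening. At SD 15 such a result is compatible with worsening beyond the lower end of the 8 to 10 range, and at SD 20 with worsening beyond the whole range.

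The documents do not support a claim that the planned size is too small for the question. Up to an SD of about 17.4, the planned 39 completers suffice for a margin of 8, and what is missing is the rule. Severity is moderate: the proof-of-principle aim limits what will be claimed, and the correction is simple.

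**What to change.** 1. Reconcile the objective and the hypothesis, so that the protocol states whether no worsening, improvement, or the first followed by the second is the primary pain question.
2. If no worsening is intended, prespecify the rule. For example: pain is judged not increased to an important degree if the lower limit of the two-sided 95% CI for mean change in KOOS Pain (follow-up minus baseline) lies above -8 points. The value -8 is the lower end of the protocol's own range and serves as illustration; the investigators must justify the margin they adopt.
3. Only if that holds, test for improvement: lower limit above 0. No alpha adjustment is needed, because the two claims are nested, tested in fixed order and read from one interval.
4. State that the sample size was set on strength alone, and give the power for pain under an assumed SD, as in the table above.
5. Always report the estimate and its CI. A worsening smaller than the margin can pass: at SD 10, an observed change of -4 has a CI of -4 ± 3.24, that is -7.2 to -0.8, which meets the margin although the worsening is significant.

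The cost is a few sentences and one confidence interval. The drawback is that a margin must be committed to in advance, with some worsening below it accepted.

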**Study Design and Methods**

This intervention study features a repeated measures design. Outcome measures will be assessed at McMaster University before and after a 12 week intervention. The yoga exercise intervention will be delivered at a yoga studio in downtown Hamilton, Ontario. This proof of principle study will aim to provide preliminary data supporting the use of a yoga exercise intervention in a sample of women with knee OA.

Participants

Fifty community-dwelling women, 50 years of age and older, who meet the American College of Rheumatology (ACR) criteria for clinical knee OA will be recruited to participate in this study. The ACR clinical criteria require 3 of the following:

- Knee pain on most days of the week,
- Less than 30 minutes of morning stiffness,
- Crepitus with active range of motion,
- Bony enlargement,
- Bony tenderness to palpation, and
- Signs of inflammation (warmth, swelling).

*Inclusion and Exclusion Criteria*

Women were selected because incidence of knee OA is two times greater among women than men over the age of 50 years (18-20). Muscle weakness is of particular concern in women with knee OA because their absolute muscle strength is lower compared to men, and therefore women are closer to the critical thresholds of strength required for activities of daily living (21). Finally, women report pain secondary to knee OA more frequently than men (20) perhaps because the pain experience is different (22). The incidence and prevalence of knee OA increases with age, particularly in women (18, 20, 23-25).

The exclusion criteria for participation include a self-reported history of patellofemoral symptoms. The exercise intervention is focused on unloading the medial knee compartment; however these exercises could place large loads on the patellofemoral joint, such as squats and lunges. In addition, participants that self-report osteoporosis will be excluded. The exercise intervention includes spinal flexion and therefore may increase the risk of a fragility fracture in the spine. Exclusion criteria include diagnosis of other forms of arthritis (e.g., rheumatoid, psoriatic); active non-arthritic knee disease (e.g., gout); conditions that might be exacerbated by the protocol (e.g., unstable angina); neurological conditions such as a stroke; and current/past use of intra-articular therapies or knee surgeries and; contraindications to magnetic resonance imaging (e.g., pacemaker). Participants will be excluded if they have a skin allergy to medical tape, use an adaptive aid such as a cane or cannot climb 2 flights of stairs safely. Lower extremity trauma within 3 months, ipsilateral hip or ankle conditions, radiation (e.g., cancer treatment) and pregnancy will also be exclusion criteria. Finally, participants that have not completed an annual physical examination by a physician in the past year will be excluded. We require this exclusion criterion to minimize the potential that participants have an underlying health condition that has not been identified or managed.

*Recruitment*

Two methods of recruitment will be used. First, participants will be recruited through a list of potential participants provided by [name] at the Centre for Appendicular Magnetic Resonance Imaging (CAMRIS) at St. Joseph’s Hospital. All of the individuals on this list have signed a consent form to be contacted for research studies. These potential participants will be identified by a receptionist at CAMRIS and a letter will be sent by the receptionist on behalf of CAMRIS inviting their participation. The letter will invite participants to email or call a research assistant if interested in the study. A research assistant will respond to potential participants using the same mode of communication. Once in contact, the research assistant will describe the purpose, protocol, risks and benefits of the study. Potential participants who express an interest will be screened for the inclusion and exclusion criteria.

Second, posters will be displayed in the Hamilton, Ontario community, including at the yoga studio. As well, the poster will be included in weekly electronic newsletters sent out by the yoga studio. The advertisement will invite potential participants to contact a research assistant via telephone or email. A research assistant will respond to potential participants using the same mode of communication. Once in contact, the research assistant will describe the purpose, protocol, risks and benefits of the study. Potential participants who express an interest will be screened for the inclusion and exclusion criteria. [name] will first meet with the potential participant at CAMRIS to confirm the presence of clinical knee OA.

For both recruitment strategies, any potential participant that expresses interest and meets the criteria for the study will be sent a copy of the consent form (electronic or hard copy at the potential participant’s discretion) and a map directing them to pre-paid parking. An appointment will be set at the MacMobilize Laboratory, McMaster University. At this time, participants will be instructed to avoid any high intensity physical activity for 24 hours prior to testing.

Yoga Intervention

The exercise intervention will be a 12-week yoga program requesting attendance at 3 supervised classes each week. Over each week, 4 classes will be available (Sunday 10-11am ; Tues, Thurs, Fri 3-4pm). Two 12-week sessions will be provided to ensure no more than 25 participants are in each session. We aim to start session one in November 2013 and session two in February 2014.

This class will be conducted at a yoga studio near downtown Hamilton in a regular temperature room (De La Sol Yoga located at the [name]; http://www.delasolyoga.com). The class will be instructed y [name]. He is a certified yoga instructor (training completed in 2008). The yoga studio is a commercial space with dedicated free parking, yoga mats and other equipment, bathroom facilities including showers, and an elevator. A structured fee is provided to the instructor and yoga studio to access space, parking and equipment. The participants will incur no costs associated with attending the yoga classes.

Each class will be 1 hour in length. The yoga class will include a warm-up period featuring large body movements with no resistance. Then the instructor will lead the class through a series of standing postures identified with our previous work as requiring high muscle activity from the knee musculature, but minimal knee adduction moment. Examples of these postures include squats, lunges, wide-legged stances in various ranges of knee motion, and balance poses. The instructor will offer a variety of modifications for each pose, to ensure that the participants have an alternative best suited for their experience level. In addition, a series of seated poses that focus on flexibility will be completed. Each class will conclude after a guided deep-breathing and meditation activity. Throughout the class, education about knee joint anatomy, osteoarthritis and proper lower extremity alignment will be included.

Retention strategies to enhance adherence to the exercise intervention will include the following:

- Exercise logbook to track activity,
- $100 stipend upon completion of the final data collection,
- Draw for $5 Tim Horton’s gift certificate at the conclusion of some classes, and
- Rewards for best attendance across 12-weeks including a 3 month yoga pass, yoga mats, water bottles.

Outcome Measures

Outcome measures will be collected at baseline and after completion of the 12-week yoga intervention. These outcome measures will be collected at the MacMobilize Laboratory (Communications Research Laboratory Building, room B110) on McMaster campus. A study limb will be chosen as the most symptomatic knee.

*Primary Outcome Measures*

*A. Strength*

The peak torque developed during knee extension and flexion during a maximum voluntary isometric contraction will be measured by use of a Biodex System 2 isokinetic dynamometer. Data will be presented as Nm/kg. After a submaximal practice, 5 maximum-effort trials of isometric knee extension, with the knee joint positioned at 65°, will be recorded. The same protocol will be repeated for isometric knee flexion. The peak value for each of knee extension and flexion will be extracted. The reliability for these data are excellent (r=0.96) (26).

*B. Pain*

- The Knee Osteoarthritis Outcome Score (KOOS) is a patient-administered, 42 item questionnaire.  Study participants are asked to answer questions on a 5-point Likert scale, which takes approximately 10 minutes to complete.  The KOOS consists of 5 subscales:  pain, other symptoms, activities of daily living (ADL), function in sport and recreation and knee-related quality of life (QOL).  The questionnaire results in a normalized score out of 100 for each subscale, where 100 indicates no symptoms and 0 indicates extreme symptoms. The questionnaire relies on subject’s recall from the previous week.

The KOOS has been used in persons 13-79 years of age. The KOOS reference values are available from various sample populations including; age/sex based samples (33) (34), active soccer players (35), and male and female patients post anterior cruciate ligament reconstruction (36). The KOOS has a high test-retest reliability demonstrated by intra-class correlation coefficients of 0.80-0.97 for the Pain subscale, 0.74-0.94 for the Symptom subscale, 0.84-0.94 for the ADL subscale, 0.65-0.92 for the Sport/Rec subscale and 0.60-0.91 for the QOL subscale in patients with knee osteoarthritis (OA) (37). The minimal detectable change values for patients with knee OA are 13.4 for Pain, 15.5 for Symptoms, 15.4 for ADL, 19.6 for Sport/Rec, and 21.1 for QOL (38). Currently, the minimal clinically important change value is suggested to be 8-10 for the KOOS, proving the scale is sensitive to change (38). The KOOS has been reported to detect change following surgical procedures including; ACL reconstruction, meniscectomy, cartilage repair procedures, tibial osteotomy, total knee replacement and non-surgical procedures including; physical therapy, as well as nutritional and pharmaceutical interventions (39). The KOOS presents an internal consistency range (Cronbach’s α) of 0.65–0.94 for Pain, 0.56–0.83 for Symptoms, 0.78–0.97 for ADL, 0.84–0.98 for Sport/Rec and 0.71–0.85 for QOL in patients with knee OA (38). The KOOS has demonstrated convergent and divergent construct validity when compared against numerous instruments including the different subscales of the Short Form-36 and the Lysholm knee scoring scale (38).

The KOOS includes the complete and original WOMAC OA Index LK 3.0 therefore WOMAC scores can be calculated in isolation. The KOOS subscales ‘Sport and Recreation function’ and ‘Quality of Life’ have been shown to be more sensitive and distinct than the WOMAC subscales ‘Pain’, ‘Stiffness’, and ‘Function’ when studied in subjects with radiographic evidence of OA who underwent a meniscectomy 21 years prior to the study (mean age = 57 years, range = 38-76) compared to age and gender matched controls (40).

*Secondary Outcome Measures*

*A. Biomechanical Analyses of Gait and 3 Yoga Postures*

Participants will change into shorts, a sports bra, and be barefoot. The participants’ height, body mass, lower limb length, anterior superior iliac spine (ASIS) distance, posterior superior iliac spine (PSIS) distance, upper thigh circumference, abdominal circumference knee width, calf circumference and ankle width will be measured. Then, 3 rigid body marker clusters will be placed on the participant with Velcro straps. These will be placed between the left and right PSIS, on the study thigh, shank and the top of the foot. These correspond to the specifications required to create a lower-body model. Landmarks will be digitized in reference to the rigid body marker clusters. These landmarks include: both left and right ASIS, iliac crest, PSIS, greater trochanter, lateral and medial distal femoral condyles, lateral and medial tibial proximal condyles, lateral and medial malleoli, tibial tuberosity, proximal fibular head, head of metatarsals 1, 2, 5, and calcaneus.

With the participants on a force plate and in the field of view of three banks of Optotrak cameras (which record only positions of the markers), a 5 second standing reference trial will be collected for the motion capture system. Participants will be instructed to perform 10 hip rotations, 5 in each direction. Participants will be instructed to perform 5 knee flexions and extensions of both legs. Participants will be asked to perform 3 yoga postures (squat, lunge and wide-legged stance) for 10 seconds with at least a 10 second rest in between each posture. The order of these postures will be randomized between participants. Finally, participants will be asked to walk across the 10 foot motion capture area. For each yoga posture and gait, 3 successful trials will be recorded.

*B. Mobility Performance Measures*

- The Six-Minute Walk Test (6MW) is used to quantify walking ability. The 6MW is an inexpensive clinical tool that involves recording the distance that participants cover while walking indoors at their own pace for 6 minutes. Participants are free to stop or use a mobility aid to complete the walking task, making this measure clinically useful. The 6MW measurement will be recorded indoors in a well-lit, tiled rectangular hallway. The score recorded is the total distance traveled in 6 minutes. Instructions for the 6MW will correspond with the published protocol (44). The 6MW yields highly reliable (intraclass correlation coefficient=.96) and valid data (45).
- Participants will be asked to ascend and descend a 9-step staircase as quickly as possible, without compromising their safety. The hand rail can be used as needed. The participants will be asked to start at the base of the stairs at a distance from the first step of their choosing. The participants will be instructed not to run or jog, and not to skip any steps. Time to ascend and descend will be recorded separately, to the nearest 10^th^ of a second, using a stopwatch. Participants will be asked to repeat this procedure two times, where scores from only the ascent and descent on the second attempt are recorded. Data from our laboratory demonstrate excellent test-retest reliability of the stair ascent and descent tasks among 29 adults (ICC=0.881, 0.843 respectively).
- The 30 second chair stand task quantifies the number of sit-to-stand movements that can be completed within 30 seconds, starting from a seated position in an armless chair of a standard height (45 cm). After an opportunity to practice the task, participants will be asked to perform this task at a comfortable pace. Knee extensor strength has been shown to be a strong predictor of performance on repeated chair stand tests (46). In addition, lower extremity muscle power was predicted from performance of the 30 second chair stand in 14 older adults (47).

*C. Cardiovascular Measures of Fitness*

- In addition, participants will be asked to complete the YMCA cycle ergometer submaximal test. Maximal oxygen uptake (VO_2_max) is regarded as the best measure of cardiovascular fitness and is a good indicator heath status (48). Unfortunately, evaluating VO_2_max is expensive, time consuming, and requires specialized laboratory equipment, trained personnel, and medical supervision for some populations. The YMCA cycle ergometer submaximal test is used to estimate VO_2_max by extrapolating submaximal data points. This test is ideal for assessing the cardiovascular fitness of individuals not accustomed to maximal intensity exercise.

The protocol includes three or more consecutive 3-minute stages at a given workload that is designed to raise the participant’s heart rate to a value between 110 beats per minute and approximately 85% of the age predicted max heart rate for two consecutive stages. The initial stage consists of a 25 Watt workload at a pedaling rate of 50 revolutions per minute, which is maintained throughout the test. The workload of subsequent stages is determined by the participant’s heart rate during the final minute of the first stage. When a heart rate between 110 beats per minute and 85% of the age predicted heart rate max is achieved at a steady state for two consecutive stages the test is terminated. Oxygen cost is estimated for the final two stages using a formula encompassing workload, body mass and derived constants. The two oxygen costs are then used to formulate a linear equation, which is extrapolated to predict the participant’s VO_2_max. The submaximal test is used by the Canadian Society for Exercise Physiology and included in the Canadian Physical Activity, Fitness and Lifestyle Approach protocol. The predicted VO_2_max values from submaximal tests have been cross-validated to the traditional gold standard methods of achieving a true VO_2_max (via maximal treadmill running). A study examining 55 men (mean age = 38.1 ± 10.7) and 47 women (mean age = 38.7 ± 9.9) found a moderate correlation (r = 0.77, p ≤ 0.05) between the predicted VO_2_max values attained from the YMCA protocol and the true VO_2_max values from a treadmill test (49). This correlation is strengthened (r = 0.90, p ≤ 0.05) when the men are removed from the calculation, suggesting the relationship may be stronger in women, making the test more appropriate for the female sample population of the proposed study (49).

Protocol

*Baseline Measures: MacMobilize Laboratory at McMaster University, Hamilton*

1. Written, informed consent
2. Anthropometric Measurements
3. Resting Heart Rate and Blood Pressure
4. Instrumentation & Biomechanical Analyses (Gait and Yoga)
5. Mobility Performance Measures
6. Strength Assessment
7. Questionnaire: KOOS
8. YMCA protocol

This laboratory visit will require 2.5 hours to complete.

*Yoga Intervention: De La Sol Yoga at [name], Hamilton*

- 12-week intervention
- Requesting attendance to 3 supervised classes each week

Each yoga class will be 1 hour.

*Follow-up Measures*

1. Anthropometric Measurements
2. Resting Heart Rate and Blood Pressure
3. Instrumentation & Biomechanical Analyses (Gait and Yoga)
4. Mobility Performance Measures
5. Strength Assessment
6. Questionnaire: KOOS
7. YMCA protocol
8. Stipend

This laboratory visit will require 2.5 hours to complete.

Sample Size Estimation

Systematic reviews of the effectiveness of resistance training for improving self-reported physical function and isometric knee strength in knee OA had average effect sizes of 2.11 and 0.41 respectively (5). Given the lower effect size (0.41) and a Type I error = 0.05 on a 1-tailed test (based on strong evidence of improvement), a sample of 39 participants is necessary to yield 80% power to detect a significant effect. We aim to recruit 45 participants to account for drop-outs and losses to follow-up.

Statistical Analyses

Descriptive statistics will be determined for all of the outcome measures. Repeated measures analysis of variance will be used to determine if changes in the primary and secondary outcome measures as a result of the yoga exercise intervention. The p value will be set at p<0.05.

